Our hypotheses are based on the following arguments. First, ADR neurofeedback training was developed specifically to restore an imbalance in excitatory/inhibitory neuronal activity in the auditory cortex in individuals with tinnitus [13] and, therefore, should be more efficacious than BTR neurofeedback. Second, the ADR protocol has been used with success to reduce distress and/or intensity in three prior studies [9, 13, 14]. Third, given the added influence of non-specific effects in neurofeedback, participants in the ADR and BTR groups will have greater expectations of treatment outcomes than participants in the diary control condition. Based on these observations, we hypothesise the following:
Participants undergoing ADR neurofeedback training will report significantly stronger reductions in tinnitus distress and intensity from pre- to post-treatment compared to participants undergoing BTR neurofeedback.Participants in both the ADR and BTR neurofeedback interventions will improve more significantly in measures of tinnitus distress and intrusiveness from pre- to post-treatment Methods/Design

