### Study Design

The study, a three-armed, randomised controlled trial, will be conducted at Philipps University in Marburg, Germany. The study has been approved by the respective ethics committees of the Department of Psychology and the Department of Medicine at Philipps University with registration numbers 2018-4 k (Additional file 2) and 162/18 (Additional file 3), respectively. Furthermore, the trial is registered with clinicaltrials.gov (ClinicalTrials.gov Identifier: NCT03550430).

Sample size calculations were based on a repeated-measures multivariate analysis of variance (MANOVA) and conducted with G*Power 3.1.9.2 [23].. The total sample size needed to detect a medium assessment-by-treatment interaction effect (*f* = 0.25, *Beta* = 0.80, *Alpha* = .05, Groups = 3, measurements = 3) is 98. However, to compensate for an estimated dropout rate of 20% during treatment, the aim is to recruit 120 participants, i.e., 40 participants per group. Post-hoc analyses are carried out between ADR vs. BTR, ADR vs. diary control and BTR vs. diary control.

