**Fig. 1 Fig1:**
[figure not shown]
Schedule of enrolment, interventions and assessments

The fourth and final stage in t0 is a standard audiological examination at the ENT-clinic at the University Hospital of Giessen and Marburg (UKGM). There are two main purposes for this visit: The first is to rule out possible non-subjective causes of tinnitus, and the second, to acquire audiometric data. At the clinic, participants first learn about the components of the audiological examination before signing the informed consent form (see Additional file 5). Subsequently, the audiological examination, in which the below information is acquired, takes place:
Standard Audiogram (to 20.000 Hz)TympanometryOtoacoustic emission (OAE)Tinnitus loudness discomfort levelTinnitus matching (loudness, pitch)

Participants who are included after the visit to the ENT clinic take the baseline assessment in the pre-allocation (t1) stage. Upon completion of this assessment, participants move to the allocation (t1) stage and are randomly assigned to one of three arms in the study: Group 1, which receives alpha/delta neurofeedback training; Group 2, which receives beta/theta neurofeedback; and Group 3, which is the diary control group.

The post-allocation (t2) intervention period lasts 4 weeks. Within this timeframe, ten neurofeedback training sessions are undertaken for the two neurofeedback groups, with a minimum of two and maximum of three sessions per week. For the diary control group, two face-to face visits to the department and two telephone calls are scheduled within the 4-week period. t2 mid-point assessments are completed 2 weeks after the start of the intervention. In the post-allocation (t3) stage, participants complete the endpoint assessment online prior to a visit to the Department of Psychology, where they complete the ANT and SART (referred to as cognitive assessment II in Fig. 1). t3 post-assessments are completed 4 weeks after the start of the intervention.

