### Statistical analysis

Data will be analysed primarily in the intention-to-treat (mITT) population. Supportive analyses are planned in the per-protocol (PP) population. mITT comprises all randomised patients, while PP analysis assesses mITT patients who show no change in their status during the trial period that violates the criteria for their inclusion/exclusion (for example, the data from someone seeking another type of treatment for their tinnitus during the trial period is excluded from further analyses).In addition, data from participants who deviate significantly from the visit schedule are excluded from analyses, and data from participants who show poor compliance during feedback sessions are excluded (e.g., showing sleepiness or lack of focus and orientation to the task). For all outcome measures, we will probe the longitudinal course across all assessments using a linear mixed model for repeated measures (MMRM, see [61]). The MMRM model includes fixed effects for group (ADR vs. TBR vs. diary control), time and group-by-time interaction, as well as a random intercept for subject specific effects using maximum likelihood estimation, adding sex, age, baseline tinnitus severity scores and patients’ expectations as covariates. The error variance-covariance matrices for the repeated factor will be specified in accordance with the data. The pattern of missing data is assumed to be random.

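### Read naturally, the primary mixed model uses the t1 score as both response and covariate, so the adjustment adds almost nothing to the group-by-time contrast

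*Protocol article*

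**What the plan says.** All references are to the protocol article.

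- **Responses.** Under Statistical analysis, for every outcome, "we will probe the longitudinal course across all assessments using a linear mixed model for repeated measures".
- **Model terms.** "The MMRM model includes fixed effects for group", time and their interaction, "as well as a random intercept for subject specific effects using maximum likelihood estimation". The covariates enter by "adding sex, age, baseline tinnitus severity scores" and patient expectations.
- **Error covariance.** It is left open: "The error variance-covariance matrices for the repeated factor will be specified in accordance with the data".
- **Schedule.** Under Procedure/trial protocol, included participants "take the baseline assessment in the pre-allocation (t1) stage". Later assessments are t2 (2 weeks), t3 (4 weeks) and t4 (4 months).
- **Hypothesis.** The Introduction states that participants in the alpha/delta arm "will report significantly stronger reductions in tinnitus distress and intensity from pre- to post-treatment compared to participants undergoing BTR neurofeedback".
- **Sample size.** Study Design powers an assessment-by-treatment interaction with "Groups = 3, measurements = 3" and arrives at 98.

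Nowhere does the article say outright whether t1 is one of the modelled responses.

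**The concern.** A group-by-time interaction expresses change from before to after treatment only if the pre-treatment score is among the responses. If it is, entering the same score again as a main-effect covariate is not baseline adjustment. A covariate that is constant over time shifts all of a participant's visits equally and cancels from any contrast between visits. The plan would appear to adjust for baseline, age, sex and expectations while its treatment test remained a plain comparison of change scores.

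For THI the covariate may be identical to the t1 response. Depending on which covariance structure is later chosen, that can make the likelihood degenerate.

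If instead only post-baseline visits are responses, the covariate is in its proper place but the interaction no longer answers the hypothesis. At stake are the precision and definition of the treatment effect for both primary outcomes.

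**Working it through.** **1. The plan's own figure.** Repeated-measures MANOVA, within-between interaction, f = 0.25, 3 groups, 3 measurements, alpha 0.05:

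- s = 2, df1 = 4, df2 = 2 × (98 − 3 − 2 + 2) = 190
- noncentrality = 98 × 2 × 0.25² = 12.25
- power = 0.8005

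The stated 98 reproduces. It uses no covariates, so nothing below changes it.

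**2. Is t1 a response?** All assessments include t1, and the hypothesis is pre-to-post change. Both point to yes. The three measurements in the sample size do not settle it. With t1 to t4 scheduled, they could be baseline and two later visits, or t2, t3 and t4.

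**3. If t1 is a response: effect of the covariate.** Write the mean for participant i in group g at time t as μ(g,t) + βx(i). In [μ(g,t3) − μ(g,t1)] − [μ(h,t3) − μ(h,t1)], the term βx cancels. Random-intercept fits to simulated data (99 participants, 4 visits, assumed rho 0.6) confirm this:

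| Data (ML fits) | Estimate (SE) without baseline | Estimate (SE) with baseline |
|---|---|---|
| Complete | 2.3326 (3.9927) | 2.3326 (3.9927) |
| 20% dropout | 7.776 (4.869) | 7.799 (4.799) |

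With complete data the adjustment is exactly inert. With dropout the SE moves by about 1.4%. The same holds for age, sex and expectations, and for TMI even if the severity covariate is THI.

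**4. Precision forgone.** For one follow-up with equal variances (in units of σ²), the change-score variance is 2(1 − rho) and the baseline-adjusted variance is 1 − rho². Their ratio is 2/(1 + rho). The documents give no pre-post correlation, so rho is assumed. The value 0.92 is the THI test-retest reliability from the Measures section, used as a high-end case.

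| rho | Change score | Adjusted | Ratio | Variance saved |
|---|---|---|---|---|
| 0.5 | 1.00 | 0.75 | 1.33 | 25% |
| 0.7 | 0.60 | 0.51 | 1.18 | 15% |
| 0.92 | 0.16 | 0.1536 | 1.04 | 4% |

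In the complete simulated data set (REML), the SE at t3 was 4.05 with t1 as response plus covariate and 3.62 with t1 as covariate only. The variance ratio is (4.05/3.62)² = 1.25, which equals 2/1.6.

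**5. Likelihood for THI under a free covariance.** With coefficient b on the baseline score, the t1 residual is (1 − b) times the centred t1 score, so its variance shrinks as (1 − b)². The log-likelihood then contains −N log(1 − b), which has no upper limit as b approaches 1. Profile values with an unstructured matrix:

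| b | Log-likelihood |
|---|---|
| 0 | −1658 |
| 0.9 | −1430 |
| 0.999 | −974 |
| 0.999999 | −290 |
| 1 − 10⁻⁹ | +393 |

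A diagonal matrix with unequal variances behaves the same way. Homogeneous random-intercept and AR(1) fits gave ordinary finite solutions. Separately, a random intercept added to an unstructured residual matrix is not identifiable.

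**6. Maximum likelihood.** SE ratio to REML at N = 98: √(95/98) = 0.985, about 1.5% too small. Type I error at a nominal 0.05 is 0.055–0.057 for a single contrast with a normal reference, 0.056–0.057 for the interaction with an F reference, and 0.060–0.061 for a Wald chi-square. REML with chi-square gives 0.054, so part of the excess comes from the reference distribution. At N = 120 the maximum likelihood figures are 0.054–0.059.

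**7. If only t2 to t4 are responses.** Suppose the group difference is d at t2, t3 and t4. Every interaction contrast is d − d = 0, so a treatment effect fully present by t2 and then maintained is invisible to the interaction.

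**The case against.** The strongest reply is that the double use is inferred. The label MMRM and the listing of baseline as a covariate both fit a model with post-baseline responses only, and the three measurements fit t2 to t4 equally well. That is fair: a reader might infer that the plan states the double use, and it does not. But the post-baseline reading meets the difficulty in step 7, so the text needs correcting either way.

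A reader might also infer that the primary analysis cannot be fitted. The documents do not support that. They name no unstructured or heterogeneous covariance, and common simpler structures give finite fits. The degeneracy also needs the covariate to equal the response. Under Randomisation, severity is graded by THI, so for TMI and the secondary outcomes the covariate may be a different score.

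Third, a change-score contrast is unbiased and matches the hypothesis as worded, and the sample size never relied on covariate adjustment. This stands: the loss is of precision, not validity. At a correlation near 0.92 it is small.

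Finally, covariance structure and degrees of freedom are often left to an analysis plan that is not shown. Their absence is therefore no fault in itself. They matter here only because of how they combine with the responses, covariates, random intercept and estimator that the article does state.

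**Conclusion.** The point holds as a correctable weakness in the stated model, not as a failed analysis. On the natural reading, the covariates do essentially nothing for the group-by-time contrast: exactly nothing with complete data, and about 1.4% on the SE in one simulated set with 20% dropout. The variance penalty against proper baseline adjustment is between 1.33 and 1.04 for an assumed rho of 0.5 to 0.92. The unbounded likelihood is a conditional risk, confined to THI with a free or heterogeneous covariance. The maximum likelihood effect is real but minor, with type I error of about 0.055–0.061 at N = 98; it does not amount to serious inflation. On the alternative reading, precision is recovered but the interaction tests the wrong thing, and the effect must be read as the adjusted group difference at t3. No inference should be drawn that the planned 98 is wrong.

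**What to change.** State whether t1 is a response, and choose one of two models:

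1. Keep t1 as a response with group means constrained equal at baseline, and remove the baseline covariate. This keeps every randomised participant, because t1 precedes allocation, and so fits the planned primary analysis set.
2. Model t2, t3 and t4 only, with the outcome's own t1 score (THI for THI, TMI for TMI) and its interaction with time as covariates.

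In either case, define the primary effect as the group difference at t3, and keep sex, age and expectations as planned. Fix the covariance structure in advance, omitting the random intercept if it is unstructured. Use REML with Kenward-Roger degrees of freedom.

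The cost is a few sentences and no extra participants. Intervals become slightly wider through REML and Kenward-Roger, and option 2 loses participants who have only a t1 score.

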### Procedure/trial protocol

Recruitment for the trial is completed primarily through advertisements placed in local and regional media. In addition, a referral programme is established to entice ear-nose-throat physicians (ENTs) to forward participants to the study. Interested individuals can read more about the study on a dedicated website, where they also can register their interest in trial participation. Both the website and the questionnaires are provided via the Iterapi platform [25].

The enrolment period (t0, see Fig. 1) is a four-stage process. In the first stage, participants complete a battery of online screening questionnaires. These are principally designed to sort individuals into eligible and non-eligible categories, based on the inclusion/exclusion criteria. Prior to taking the screening questionnaires, participants will give informed consent for questionnaire completion only. For principally eligible individuals, the second stage in the screening process is a telephone interview. The purpose of this is to validate questionnaire responses and to assess their motivation to participate in such a trial. The third stage in t0 is a visit to the Department of Psychology. The first part of this visit provide participants with detailed information about the study, its procedures and how to complete baseline assessments, including primary and secondary outcome measures on the secure online platform. Following this, participants sign the informed consent form (see Additional file 4) and complete the State Anxiety Inventory online (STAI) [26]. Participants then complete two attention tests, the Attention Network Task (ANT) [27] and the Sustained Attention to Response Task (SART) [28], referred to in Fig. 1 as the cognitive assessment.

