### Randomisation

When, as in our study, specific prognostic factors may influence outcomes, the best way to ensure a balanced distribution of participants across groups is to use an allocation by a minimisation process [30]. Accordingly, participants are stratified to one of the three study groups according to on their age and the severity of their tinnitus [31]. Age is included as a prognostic factor. This is based on the assumption that neurofeedback utilises the brain’s ability to reorganise itself functionally and/or structurally [32, 33]. With the current knowledge, evidence favours the hypothesis that younger individuals have greater neuroplastic potential [34] compared to older individuals. This is partially because of the association between increasing age and functional and structural brain deterioration [35, 36]. However, it would be false to believe that this deterioration affects all individuals to the same degree. With increased age comes large individual differences in brain health [34]. These differences are already apparent by the time people reach their mid-fifties [35]. Taken together, these observations have led to the following stratification categories for age in the present study: 1) ≤ 55 years; 2) > 55 ≤ 64; 3) > 64 ≤ 69; and 4) > 69. Given the conservative inclusion criterion on the primary outcome variable (18 ≥ THI score pre-intervention ≤100), stratifying participants into sub-groups based on the tinnitus distress classification by McCombe and Baguley [31] is considered a sensible option. This ensures a balanced distribution of the range of THI scores across the three groups. Importantly, this reduces the risk of heterogeneity of variance affecting the between-group outcome analysis. Thus, participants are stratified to one of four levels of tinnitus distress: 1) mild (THI 18–36); 2) moderate (THI 38–56); 3) severe (THI 58–76); and 4) catastrophic (THI 78–100).

Allocating participants to one of the three groups is performed by a researcher independent of the study. This individual, trained in the minimisation programme Minim [37], will subsequently inform the research team about the group allocation of each participant. A group allocation list is kept in a separate and password secured Excel file on the local drive of the independent researcher’s PC.

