#### Measures

##### Primary outcome measures

There are two primary outcome measures in the study. First, the change in tinnitus distress following neurofeedback training is measured with the THI [24]. The THI is a 25-item self-report instrument. Each item is rated on a three-point Likert scale with responses of ‘Yes’ = 4 points, ‘Sometimes’ = 2 points, and ‘No’ = 0 points, thus yielding a total score between 0 and 100. The instrument has three subscales, assessing functional, emotional and catastrophic reactions to tinnitus. The overall test-retest reliability of the scale is 0.92 [46]. It has been translated and validated into a German version [47, 48], which is used in the present study.

To assess the efficacy of neurofeedback training in reducing the perceived intensity, i.e., the sound perception of tinnitus, the TMI is used [49]. This is a three-item measure designed to assess the individual perception of tinnitus sound intensity, without overlapping significantly with cognitive, behavioural or emotional reactions to tinnitus. The internal consistency of the scale is excellent, with Cronbach’s α = 0.86; it also has satisfactory discriminant validity (correlation of *r* = .62 with the THI). One obstacle in the development of the TMI, noted by Schmidt and Kerns [49], is the differential scaling of its three items. This has, according to the authors, the potential to increase measurement error. Schmidt and Kerns [49] suggested converting the three items into a standardised scale. Consequently, in the present study, the response scales for all three items are standardised to a range from 0 to 100.

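### The model takes each outcome's own t1 score as a response, not a covariate, so the week-4 contrast is a difference in change and less precise than own-baseline adjustment

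*Protocol article*

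**What the plan says.** The Statistical analysis section of the protocol article gives a single model: "For all outcome measures, we will probe the longitudinal course across all assessments using a linear mixed model for repeated measures". Its fixed effects are group, time and their interaction, "as well as a random intercept for subject specific effects using maximum likelihood estimation". One covariate list serves every outcome: "adding sex, age, baseline tinnitus severity scores", together with expectations.

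The severity score is not defined there. The Randomisation section uses tinnitus severity to mean THI bands: "participants are stratified to one of four levels of tinnitus distress". On that usage the baseline score in the model is the THI.

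The Abstract defines the primary outcomes as between-group differences in change at 4 weeks, and the hypotheses in the Introduction are framed from before to after treatment. Every outcome is measured before allocation. The Procedure/trial protocol section refers to "baseline assessments, including primary and secondary outcome measures on the secure online platform" and places the t1 assessment ahead of randomisation. The section does not say outright whether t1 is a response or only a baseline.

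**The concern.** A measure's own pre-randomisation value is usually the best single predictor of its later value. Each t1 score is collected here, but the covariate list names only tinnitus severity. That phrase cannot naturally cover the ISI or PHQ-9.

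With t1 among the responses, the t1 score is not ignored. It enters by subtraction, because the group-by-time contrast at week 4 compares changes from t1. Subtracting the whole baseline over-corrects whenever the correlation between t1 and week 4 is below 1. Regression adjustment removes only the part that predicts the outcome and so gives a smaller variance. At stake is the precision of the week-4 contrasts, above all alpha/delta against beta/theta neurofeedback on the two primary outcomes.

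**Working it through.** **The plan's own figure.** The Study Design section gives a total of 98 for f = 0.25, power 0.80, alpha .05, 3 groups and 3 measurements (repeated-measures MANOVA). With the Pillai trace, s = 2, df1 = 4, df2 = 2(N-3) and noncentrality N × s × f², N = 98 gives noncentrality 98 × 2 × 0.0625 = 12.25 and power 0.8005. N = 97 gives 0.796. The figure reproduces and does not depend on which baseline is adjusted for. With 40 per arm and 20% dropout, 40 × 0.8 = 32 per arm remain.

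**Inputs assumed.** rho, the t1-to-week-4 correlation, is not given for any outcome; 0.5 to 0.8 is used. Also assumed are equal variances, a common correlation between visits, complete data and, for power only, a 0.5-SD difference between two arms.

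**Formulas.** With outcome SD 1 and n per arm, the contrast variance is 2v/n.

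- t1 as a response (difference in change): v = 2(1-rho).
- Own t1 as covariate, later visits as responses: v = 1-rho².
- Ratio of the second to the first: (1+rho)/2.

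| rho | change, 2(1-rho) | own baseline, 1-rho² | variance cut | SE cut |
|---|---|---|---|---|
| 0.5 | 1.00 | 0.75 | 25% | 13% |
| 0.6 | 0.80 | 0.64 | 20% | 11% |
| 0.7 | 0.60 | 0.51 | 15% | 8% |
| 0.8 | 0.40 | 0.36 | 10% | 5% |

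**Power.** Power = Φ(0.5/√(2v/n) - 1.96). At rho 0.7 and n = 32:

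- change: √(2 × 0.60/32) = 0.194; 0.5/0.194 - 1.96 = 0.62; power 73%.
- own baseline: √(2 × 0.51/32) = 0.179; 0.5/0.179 - 1.96 = 0.84; power 80%.

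With 40 per arm the same formula gives 82% and 88%.

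**What the listed covariate does.** A covariate that is constant over time and entered as a main effect cancels from a within-person change when data are complete. A simulation of 4,000 trials (three arms of 32, TMI at t1 to t4, rho 0.6, random-intercept model) confirmed this. With t1 as a response, the SD of the week-4 contrast was 0.224 with the THI as covariate, with no covariate, and with own t1 as covariate; the estimates agreed to rounding error. With t2 to t4 as responses and own t1 as covariate, the SD fell to 0.202, a variance cut of about 19% against 20% by formula.

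**Making only half the change.** Suppose t1 left the responses while the THI stayed the only baseline covariate. For the TMI, take the reported THI correlation of .62 (Primary outcome measures) and assume a cross-lagged correlation of .62 × rho. Then v = 1-(0.62 × rho)² = 0.904, 0.862, 0.812 and 0.754 for rho 0.5 to 0.8. From rho 0.6 upward this is worse than the change contrast. Own-baseline adjustment would cut these variances by 17%, 26%, 37% and 52%. Power at rho 0.7 with 32 per arm would be 60%.

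**The case against.** The strongest defence is that the model is valid and common. It uses each outcome's own t1 score, estimates change as the hypotheses describe it, and does not bias the randomised comparison. The gain depends on a correlation the document does not give, and shrinks as that correlation rises. If the PHQ-9 test-retest value of 0.84 is taken as its rho, the standard error falls by only about 4%. The plural in the severity covariate could also cover the TMI and TFI, and covariate coding per outcome is often left to an analysis plan that is not shown here. All of this limits the size of the point. It does not remove it: the article states its model and covariate list, and under the natural reading that model gives the less precise contrast even if severity includes the TMI, because a main-effect covariate adds nothing while t1 is a response.

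A reader might infer something stronger: that the t1 scores of the TMI, ISI and PHQ-9 go unused, that chance baseline imbalance in them stays largely in the estimate, and that the loss is 17% to 52% of the TMI variance. The text does not support this. Modelling all assessments with group-by-time, and defining the effect as change, makes t1 a response, so any t1 difference between arms is subtracted. The larger figures need a model of post-baseline visits only, which the article does not describe. Nor is the loss confined to outcomes other than the THI: the THI contrast is also a difference in change, with its t1 score both a response and a covariate.

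**Conclusion.** The point holds as a moderate loss of precision. On the natural reading, the week-4 contrast for the THI, TMI, TFI, ISI and PHQ-9 has a variance proportional to 2(1-rho) where 1-rho² is available from data already collected. Own-baseline adjustment would remove 25% to 10% of that variance for rho from 0.5 to 0.8. In the example of a 0.5-SD difference at rho 0.7 with 32 per arm, that is about 7 percentage points of power. These figures rest on the assumed rho, equal variances and complete data. There is no bias, and the total of 98 stands apart from this. The change is worth making because it is nearly free and the trial expects only about 32 completers per arm for its main comparison.

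**What to change.** In Statistical analysis, make two edits together:

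1. State that t2, t3 and t4 are the responses and t1 is not.
2. Replace the single severity covariate with the t1 score of the outcome being analysed, with its interaction with time. Keep age and baseline THI in every model as the minimisation factors; for the THI outcome, baseline THI is already its own t1 score.

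An equivalent choice in principle is to keep t1 as a response and constrain the group means to be equal at t1.

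Neither edit works alone. Adding own t1 as a main effect while t1 stays a response gains nothing. Removing t1 from the responses while the THI stays the only baseline covariate makes the TMI contrast less precise than now at rho 0.6 or above, under the cross-lag assumption in the working.

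The cost is a few degrees of freedom per model and a short change of wording, with no new data. Under the covariate version, participants with no post-baseline score do not contribute.
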